### Intervention

#### Development of intervention

The multimedia intervention developed in this study will involve dissemination of knowledge of CRC and the importance of CRC screening to South Asian dyad participants via a combination of intervention materials including a PowerPoint presentation, a video clip and a health information booklet. Prior to the development of these materials, an advisory panel will be formed, comprising health professionals, a community centre leader, a representative of a South Asian association, a health leader who has been involved in cancer prevention for South Asians, our research team and the acting group, and a script writer. Panel members will meet to discuss what health information to include in the intervention and the strategies required to enhance the cultural sensitivity of the intervention, as well as the linguistic appropriateness and clarity of intervention materials. Panel members will be asked to make recommendations on such strategies.

The development of intervention contents will be guided by the Health Belief Model (HBM), a widely used conceptual framework for developing strategies that induce behavioural changes in chronic disease prevention [30]. For the present intervention, a PowerPoint presentation will first be prepared and presented during the health talks arranged as part of the intervention. The presentation will consist seven sections, namely 1) what is colorectal cancer? 2) risk factors, signs and symptoms, 3) myths and misconceptions, 4) measures for prevention and early detection of CRC, 5) procedures of stool sample collection using a FOBT kit, 6) CRC screening pilot scheme and other service providers in Hong Kong, and 7) implications of a positive test and progression to colonoscopy. After that, a health information booklet will be produced. The PowerPoint presentation will be written in English, while the booklet will first be written in English and later translated into Urdu, Nepali and Punjabi. Advisory panel members and six South Asians (two Indians, two Nepalese and two Pakistanis) as lay persons will be consulted to give feedback on whether the materials present health information in a clear manner, and whether the contents are culturally relevant as well as linguistically appropriate.

A video clip will also be produced based on the storyline and script drafted by the script writer. The aim of the video clip is to highlight the role of younger family members in increasing older South Asian adults’ intention to engage in healthy behaviours. Feedback on clarity and linguistic quality of the script will be sought from the advisory panel members and the six South Asian lay persons. To enhance the cultural sensitivity of the video clip, South Asians will be employed as actors and actresses in the video clip production. Appropriate settings will also be arranged for video shooting, such as the home of a South Asian volunteer and a health clinic. Actors will speak in English during video shooting, after which the video will be dubbed into Hindi with English subtitles.

#### Delivery of intervention

The intervention will involve the assessment of the proportion of dyad participants who undergo FOBT conducted by a family doctor in each group. Prior to the introduction of intervention, our research team will access a list of family doctors enrolled in the CRC screening pilot programme. Family doctors based in the ten chosen districts will be contacted via mail, where the research team will provide an introduction to the aims of the study and request for their consent of collaboration, so that dyad participants can be referred to the consented doctors for FOBT.

Our research team will contact partner organizations in districts allocated as the intervention group for logistical arrangements concerning intervention delivery. During intervention, a health talk will first be held by an intervention instructor hired by the research team. An interpreter will be on hand to provide translations if the instructor can only communicate in English. During the talk, the video clip will be shown to dyad participants, alongside a demonstration on the procedures of stool sample collection for FOBT. Each dyad will then receive a health information booklet at the end of the talk.

For each dyad, a medical appointment for FOBT will be scheduled with a family doctor within 1 month after receiving the intervention. For dyads who express willingness to undergo FOBT, a representative from the partner organizations will be assigned to accompany them in the visit to family doctor for the test and the return stool sample.

#### Wait-list control group

Dyads recruited in districts allocated as the wait-list control group will receive the intervention described above within 2 months after the completion of post-intervention data collection.

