**Methods:**

A cluster randomized controlled trial will be carried out. Three hundred and twenty South Asian dyads, comprising an older adult aged between 50 and 75 and a younger family member aged between 18 and 49, will be recruited in ten districts in Hong Kong through community organizations that provide support services for South Asians in local communities. Dyads will be randomly allocated to either the intervention or wait-list control group. Intervention dyads will receive intervention, whose contents are based on the health belief model, via multiple forms of media including PowerPoint presentation, video clip and health information booklet. Control dyads will receive intervention after post-intervention data are collected. For dyads in both groups, an appointment with a family doctor will be arranged for those willing to undergo FOBT. Outcomes will be assessed at baseline and post-intervention. Data will be analysed using the Generalised Linear Models Procedure in an intention-to-treat manner.

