### Subject recruitment

Recruitment of South Asian dyads will be carried out at partner organizations within local communities in Hong Kong. Prior to the implementation of intervention, our research staff will approach potential partner organizations to seek their support in subject recruitment. These organizations will be asked to distribute a subject recruitment notice amongst their South Asian members in form of posters and social media posts. Persons-in-charge of these organizations will also be invited to contact their members for taking part in the study. Permissions to recruit potential dyads during the social activities under partner organizations will also be sought. Potential dyads interested in joining the study will be screened for eligibility before enrolment.

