### Randomization

A cluster randomization approach will be utilized in this study. In previous community-based projects, we had identified ten districts in Hong Kong populated with a large number of South Asians. These districts will be randomized into either the intervention or wait-list control group, with five districts allocated to each group respectively. Partner organizations located in each district will be allocated to either group based on the outcome of group allocation of respective districts. Sealed and numbered envelopes will be used during group allocation to ensure concealment. To ensure successful recruitment of 320 dyad participants for the study, we aim to recruit 50–60 dyad participants in each district.

Randomization will be conducted by a research staff member independent from the research team so that outcome assessors and study investigators will be blinded to group allocation. However, owing to the use of a wait-list control group in this study, it will not be possible to blind the dyad participants.

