### Data collection procedures

Upon receipt of the informed consent, dyad participants will be asked to complete the author-developed questionnaire for the collection of demographic data (T0). At baseline and immediately after the intervention (T1), younger family members of the dyads will be asked to complete the questionnaire that assesses their willingness to encourage older family members to undergo FOBT and their readiness to assist them in collecting stool samples for the test. At T1, dyad participants will also be asked to complete the satisfaction questionnaire to indicate their level of satisfaction of the intervention. A coordinator from our research team will prepare an attendance record, recording the number of older family members of the dyads who attend medical consultation at a family doctor a month post-intervention (T2) and return the stool sample to the family doctor for FOBT 2 months after the medical consultation (T3). Data collection from the dyads in the control group will also be conducted as described above. After project completion, data collectors will approach the persons-in-charge of partner organizations for the completion of a questionnaire enquiring their level of willingness to continue implementing the intervention at their centers.

As a token of appreciation to the dyads’ participation in the intervention, our research team will offer all participants a weighing scale upon completion of baseline data collection.

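### The blinding statement does not fit the research team's own tasks, and the protocol does not fix whether dyads consent before their district's arm is known

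*Protocol article*

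**What the plan says.** **Unit of randomisation.** Under Randomization: "These districts will be randomized into either the intervention or wait-list control group, with five districts allocated to each group respectively". The organisations follow their district: "Partner organizations located in each district will be allocated to either group based on the outcome of group allocation of respective districts". Sealed envelopes are used for this step.

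**Blinding.** The same section has a staff member from outside the research team randomise, so that "outcome assessors and study investigators will be blinded to group allocation". It states openly that dyads cannot be blinded.

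**Who does what afterwards.** Under Delivery of intervention: "Our research team will contact partner organizations in districts allocated as the intervention group for logistical arrangements concerning intervention delivery". The team also hires the instructor. Under Data collection procedures: "A coordinator from our research team will prepare an attendance record". That record covers attendance at the family doctor (T2) and return of the stool sample (T3).

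**Recruitment.** Under Subject recruitment, organisations circulate a notice, and "Persons-in-charge of these organizations will also be invited to contact their members for taking part in the study". Research staff may also recruit at the organisations' social activities. The approach to organisations is dated only as before the intervention.

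**Order of recruitment and allocation.** The Wait-list control group section says "Dyads recruited in districts allocated as the wait-list control group will receive the intervention". The abstract, after describing recruitment, says "Dyads will be randomly allocated to either the intervention or wait-list control group".

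**The concern.** There are two linked problems.

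First, having an independent person randomise protects how the sequence is produced and concealed. It does not keep the result from people who must then act on it. A team that organises talks by arm knows the arms, and the protocol takes the keeper of the outcome record from that team.

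Second, in a cluster trial the envelopes conceal the allocation of districts, but selection happens when a head of organisation or a staff member invites a family and the family agrees. Every organisation in a district shares one arm, so anyone who learns that arm knows it for every later recruit there. If consent follows, families already inclined to screen may join more readily where the talk is offered now than where it is deferred. The arms could then differ in screening inclination before any talk is given, and that difference would be counted as an effect on FOBT uptake.

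**Working it through.** **1. Blinding: the sections side by side**

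- Randomization gives one reason for the blinding, namely that the person who randomises is independent.
- Delivery of intervention requires the research team to know which districts are in the intervention arm.
- Data collection procedures places the T2 and T3 record with a coordinator from that team.

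The reason given does not lead to the conclusion drawn, because at least part of the research team must know the arms. The document says neither that the coordinator takes part in delivery nor that the two roles are kept apart.

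**2. Order of consent and allocation**

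- Pointing to allocation first: the Wait-list control group wording, together with districts that were identified in advance and randomised as units.
- Pointing to recruitment first: the abstract. It is weak evidence on order, because it also describes dyads as the unit allocated, which disagrees with Randomization.
- Neutral: Subject recruitment, which fixes timing only relative to the intervention.
- Not available: the SPIRIT figure and checklist, either of which might show the order.

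The order is therefore implied but not fixed. No described step keeps recruiters or dyads unaware of the arm until consent. Ethical considerations has the detailed procedures explained before enrolment, so a dyad approached after allocation might learn then whether its talk is immediate or deferred.

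**3. What the analysis would correct**

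Data analysis compares doctor attendance and FOBT uptake by chi-squared test. Adjustment for confounders is stated only for the younger members' two repeated outcomes. Screening uptake is the outcome behind the sample size, and its comparison is unadjusted. The listed demographic items do not include prior screening.

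**4. The plan's own figures**

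126 / (1 − 0.20) = 157.5, so 158 per arm; the plan states 160. No figure is disputed here. The 126 cannot be uniquely reproduced because the two arm rates behind the 16.2-point difference are not given. It is attainable: a two-sided 5% test with 80% power gives 126 at a lower rate of about 22.2–22.5% without continuity correction, or 17.6–17.9% with it.

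**5. Illustration of possible size (all rates are assumptions, none from the documents)**

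Assume no true effect, uptake of 50% in motivated dyads and 5% in others, and a motivated share m of 20% in the control arm. Expected uptake is 0.50m + 0.05(1 − m).

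- Control, m = 0.20: 0.100 + 0.040 = 0.140.

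| m, intervention arm | Uptake | Spurious difference | Share of 16.2 | Chance of a significant result in that direction |
|---|---|---|---|---|
| 0.30 | 0.150 + 0.035 = 0.185 | 4.5 points | 4.5/16.2 = 28% | about 0.19 |
| 0.40 | 0.200 + 0.030 = 0.230 | 9.0 points | 9.0/16.2 = 56% | about 0.55 |
| 0.50 | 0.250 + 0.025 = 0.275 | 13.5 points | 13.5/16.2 = 83% | about 0.85 |

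The last column is the usual normal approximation for two proportions with 160 per arm, two-sided 5%, ignoring clustering. For the middle row: (0.09 × √160 − 1.96 × √(2 × 0.185 × 0.815)) / √(0.14 × 0.86 + 0.23 × 0.77) = (1.138 − 1.076) / 0.545 = 0.114, and Φ(0.114) = 0.545. With equal motivated shares the difference is zero.

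**The case against.** **On recruitment.** No section says that dyads enrol after allocation. The wait-list sentence is about delivery and would read naturally whichever step came first, and the timeline would normally sit in the SPIRIT figure, which is not shown. This stands. A reader might infer that recruitment certainly follows allocation, that the envelopes conceal nothing, or that randomisation no longer protects the comparison. The documents do not support any of these as fact; each depends on the arm being known before consent.

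Several features also weaken the pull to join one arm. Subject recruitment mentions a single notice with no arm-specific version. Both arms eventually receive the intervention, and the abstract offers the doctor's appointment to both. The Reach records of dyads approached and consented would allow consent to be compared by arm if tabulated that way. Younger members' willingness and readiness are measured at baseline. These points moderate the risk without removing it: the offer still differs between now and later, and the baseline ratings are not used in the planned uptake test.

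**On blinding.** The blinded roles are assessors and investigators, whereas delivery is assigned to the team at large, and no section says that one person does both tasks. Under Effectiveness, FOBT completion rests on doctors' records and samples received, which leaves little room for judgement. This limits the likely bias. However, Data analysis describes the T3 outcome as reported by the older members, so the source is not entirely settled. The statement is in any case broader than the assigned tasks allow.

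**Conclusion.** The point holds in two parts of different strength.

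The blinding part is firm. The Randomization section claims more than independent randomisation can deliver, and it must be reconciled with Delivery of intervention and Data collection procedures. This does not show that the outcome record will be biased.

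The recruitment part is a well-supported inference. The order of consent and allocation is not fixed, the wording leans towards allocation first, the abstract leans the other way, and no safeguard at the point of consent is described. Randomisation therefore may not protect the unadjusted uptake comparison if dyads enrol once the arm is known.

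The documents supply no estimate of the size. The 4.5 to 13.5 points above rest on assumed uptake rates and assumed enrolment imbalance. They show that a problem of this kind could matter against a planned 16.2 points, and they are not evidence that it will occur. The change should be made, because it is cheap and acts on a bias that the planned uptake test does not address.

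**What to change.** **Subject recruitment and Randomization.** State the order. Require that consent, enrolment and the T0 questionnaires are completed in a district before its allocation is opened. If that is not feasible, use recruiters who do not know the arm. In either case use the same invitation in both arms. Align the abstract so that districts are named as the unit allocated.

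**Randomization, blinding statement.** Limit it to roles that can be blinded. State that the delivery team is not blinded. As far as existing staff allow, whoever compiles doctor visits and stool samples should be separate from delivery. Give the analyst coded arm labels. Coding may not blind the person who extracts the records, since the doctors are based in the same districts, so the text should not promise that.

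**Cost.** Wording and sequencing, plus a wait between enrolment and the talk. The wait is longer if all ten districts are opened together. Opening them one at a time shortens it, but with a fixed five-to-five split the last allocations can be deduced once five districts of one arm have been opened.

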### Outcome measures

The outcomes of this study can be classified into five categories based on the RE-AIM framework for the evaluation of the intervention.

#### Reach

The ‘Reach’ of the intervention will be assessed by the recruitment rate, retention rate and the proportion of eligible dyad participants who received and completed the intervention in relation to the targeted sample size of 320 dyads. A record on the number of potential dyad participants approached during subject recruitment, the number of eligible dyads consented to participate in the intervention and the number of dyads who have eventually completed the intervention will be kept for the assessment of the above parameters.

#### Effectiveness

The ‘Effectiveness’ of the intervention will be assessed by three parameters:First, the research team will evaluate the proportion of dyads with younger family members (aged between 18 and 49) who are willing to encourage their older family members (aged between 50 and 75) to undergo FOBT through family doctors and ready to assist older adults in stool sample collection for FOBT. The level of willingness and readiness will be assessed using an author-developed questionnaire, where younger family members will rate items based on a five-point rating scale. The ratings obtained from intervention and control dyads will be compared subsequently.Second, the research team will also assess the proportion of dyads with older family members (aged between 50 and 75) who have consulted a family doctor for FOBT, completed FOBT and sent their stool samples to the family doctor. A record on the number of older family members of the dyads who have visited family doctor for FOBT will be accessed and the number of stool samples received by the participating family doctors will be recorded. The research team will compare the proportion of participants in the intervention and control dyads who have completed FOBT and provided their stool samples to a family doctor.Third, the research team will assess the intervention dyads’ level of satisfaction of the intervention using an author-developed satisfaction questionnaire with a five-point rating scale.

#### Adoption

The ‘Adoption’ of the intervention will be assessed by the proportion of partner organizations agreed to promote and implement our intervention against those approached during the promotion of the intervention. For this purpose, the number of partner organizations approached for the promotion of intervention and that of those agreed to help promote and implement the intervention will be recorded.

Further, the proportion of family doctors enrolled in the CRC screening pilot programme agreed to be engaged in our intervention will also be assessed by recording the number of family doctors approached for their consent to participate in the project against the number of those agreed to be engaged.

#### Implementation

The ‘Implementation’ of the intervention will be assessed by the number of multimedia interventions delivered at partner organizations and the number of visits arranged for older family members of the dyads to consult family doctor. A record on these two parameters will be kept for the assessment.

#### Maintenance

The ‘Maintenance’ of the intervention will be assessed by the level of willingness for persons-in-charge of partner organizations to continue implementing our intervention at their centers after project completion. An author- developed questionnaire with a five-point rating scale will be used for the assessment.

Demographic data, including age, ethnic group, number of people in the household, monthly household income, years of formal education, marital status, employment status, number of years’ residence in Hong Kong, family history of cancer, health insurance status, acculturation and relationship of the dyad members, will also be collected by means of an author-developed questionnaire.

All questionnaires used in outcome measurement will first be developed in English and subsequently translated into Urdu, Nepali and Punjabi by our research staff member of a South Asian origin. Back-translation will be conducted to ensure content and semantic equivalence in the translated questionnaires. A panel consisting of individuals fluent in Urdu, Nepali or Punjabi, and those involved in educating South Asians on health promotion and cancer prevention will be invited to proofread the Urdu, Nepali and Punjabi versions of the questionnaire to ensure the validity of the contents.

### Data collection procedures

Upon receipt of the informed consent, dyad participants will be asked to complete the author-developed questionnaire for the collection of demographic data (T0). At baseline and immediately after the intervention (T1), younger family members of the dyads will be asked to complete the questionnaire that assesses their willingness to encourage older family members to undergo FOBT and their readiness to assist them in collecting stool samples for the test. At T1, dyad participants will also be asked to complete the satisfaction questionnaire to indicate their level of satisfaction of the intervention. A coordinator from our research team will prepare an attendance record, recording the number of older family members of the dyads who attend medical consultation at a family doctor a month post-intervention (T2) and return the stool sample to the family doctor for FOBT 2 months after the medical consultation (T3). Data collection from the dyads in the control group will also be conducted as described above. After project completion, data collectors will approach the persons-in-charge of partner organizations for the completion of a questionnaire enquiring their level of willingness to continue implementing the intervention at their centers.

As a token of appreciation to the dyads’ participation in the intervention, our research team will offer all participants a weighing scale upon completion of baseline data collection.

